## Abstract

**Background:**

Atrial fibrillation (AF) is one of the most common cardiac arrhythmias and can lead to heart failure (HF), stroke, pulmonary embolism (PE), and other complications, seriously affecting people’s quality of life and health. Western medicine is limited in the treatment of AF, while Traditional Chinese Medicine (TCM) has unique advantages, such as less side effects, low toxicity, long effect duration, and high compliance. The prescription of HTDJ is a common prescription for the treatment of atrial fibrillation in Longhua Hospital, Shanghai University of Traditional Chinese Medicine. It has been used for many years and has a large number of clinically effective cases. It has a good clinical application prospect, but there is a lack of effective evaluation of its clinical efficacy.

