There is no name of AF in ancient TCM books. According to clinical symptoms and signs, AF should be classified as “palpitation,” and “shocking palpitation.” Since the book of “Huangdi Neijing” was published, doctors of different generations have discussed palpitation, and a variety of prescriptions have been recorded to be used for the treatment of palpitation, such as Zhigancao Decoction, Erchen Decoction, and Taoren Honghua Decoction. It is found that TCM has a certain curative effect in reducing ventricular rate, increasing cardioversion rate and improving cardiac function and its clinical symptoms [6]. [name], a professor of Shanghai Traditional Chinese Medicine in Longhua Hospital, has been engaged in various cardiovascular diseases including arrhythmia and AF for a long time. He has accumulated rich experience in clinical practice. The prescription of “Huatan Dingji Decoction”(HTDJ) for resolving phlegm and resolving palpitation is a prescription for the main syndromes of qi deficiency and phlegm opacities created by [name], one of his students, according to [name] academic idea, and combined with long-term clinical treatment experience. The whole recipe is composed of pinellia ginger, tangerine peel, astragalus root, atractylode rhizome, Poria, Coptis chinensis, cinnamon, keel, oyster, Radix ophiopogonis, Chinese date, Epimedium, and sophora flavescens. The prescription has a definite effect on the treatment of heart palpitation. A large number of related patients have taken this prescription for a long time, but it is limited to individual clinical cases and lacks a relevant evidence-based summary. Therefore, the purpose of this study was to evaluate the efficacy and safety of “HTDJ” in the treatment of AF with western medicine, to provide evidence-based medical evidence of short-term and medium-term clinical efficacy of integrated Chinese and Western medicine in the treatment of AF on the basis of TCM syndrome differentiation, and to lay a foundation for further clinical development and application.

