### Eligibility criteria

Eligible patients will be those who fulfill all of the following inclusion criteria and who do not have any of the listed exclusion criteria. The planned enrollment period is 12 weeks.

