### Inclusion criteria

The inclusion criteria are as follows: (1) The patient’s age is 18–85 years; (2) atrial fibrillation, seizure frequency ≥2 times a month (at least one ECG diagnosis); (3) the main syndrome of TCM syndrome differentiation was Qi deficiency-caused phlegm stagnation; and (4) have a correct understanding of the significance of the study, have good compliance with the observation and evaluation of the researcher, and voluntarily accept the clinical trial and fill in the clinical consent form.

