### Interventions

Eligible patients will be randomized to either the treatment group or the control group. The treatment group was treated with HTDJ plus western medicine. The control group was treated with placebo granules plus western medicine. Western medicine includes cardioversion drugs and heart rate control drugs, as well as myocardial energy metabolism drugs, must be in keeping with “the 2015 Atrial Fibrillation: Current Understanding and Treatment Recommendations.” The HTDJ and placebo were produced and packed in a single batch (production batch number: HTDJ: 1070649; Placebo: 1070649) by Shanghai Wan Shicheng Pharmaceutical Co., Ltd, which has no conflicts of interest relevant to this study. The test results of drug quality were consistent with the Chinese Medicine Standards of the State Food and Drug Administration. The placebo is composed of 10% crude HTDJ and 90% starch, which have the same appearance and scent as the active treatment drugs. Participants will take one bag twice a day for 4 weeks, while avoiding oral administration of other Traditional Chinese Medicine for efficacy evaluation. Then, do not accept Traditional Chinese Medicine, only western medicine treatment, followed up for 8 weeks, another clinical evaluation.

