### Research process record points

The subject content and data at each time point, according to the patient’s hospitalization period, will be recorded as shown in Table 1. Specifically, the screening period (−3~0 days) will be 0 to 3 days before recruitment. The 4-week treatment period was planned in two cycles of 2 weeks, with a return visit between cycles to check for AEs and monitor compliance. All interventions will be stopped after 4 weeks. Follow-up will be conducted on weeks 4 and 12. The detailed information is shown in Table 3.

**Table 3 Tab3:** Research flowchart

Activity	Phase(time points)	Screening stage	baseline period	intervention	Follow-up	
		−3d~0d	0d	4w	8w	12w
**Enrolment**	Sign informed consent	✔				
	Inclusion and exclusion criteria	✔				
	Demographic data	✔				
	Medical history and treatment history	✔				
	Basic data collection	✔				
**Outcome assessment**	Frequency of atrial fibrillation		✔	✔	✔	✔
	ECG and Holter		✔	✔	✔	✔
	Ultrasonic cardiogram		✔	✔	✔	✔
	TCM clinical syndrome integral		✔	✔	✔	✔
	Rate of increase and decrease of anti-arrhythmia western medicine		✔	✔	✔	✔
	NT-proBNP		✔			✔
	Hamilton Anxiety Scale		✔	✔	✔	✔
	Hamilton Depression Scale		✔	✔	✔	✔
	SF-36		✔	✔	✔	✔
	PVO		✔	✔	✔	✔
	Anaerobic threshold		✔	✔	✔	✔
**Safety assessment**	Physical examination		✔	✔	✔	✔
	Blood routine examination		✔	✔		
	Urine routine and urinary sediment		✔	✔		
	Liver function		✔	✔		
	Renal function		✔	✔		
	Blood lipid		✔	✔		
	GLU		✔	✔		
	INR		✔	✔		
	CHA2DS2-VAS		✔	✔		
	HAS-BCED		✔	✔		
**Other information**	Randomization	✔				
	Hemorrhage		✔	✔	✔	✔
	Readmission		✔	✔	✔	✔

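### Current users of HTDJ or other oral herbal medicine can enter with no pre-baseline rule; for them the primary comparison is continuation against reduction, not the effect of adding HTDJ

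*Protocol article*

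**What the plan says.** Use at the site. The abstract's Background states: "The prescription of HTDJ is a common prescription for the treatment of atrial fibrillation in Longhua Hospital". The Introduction adds: "A large number of related patients have taken this prescription for a long time". Study design and settings and Recruitment name the same hospital as the only source of participants.

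Eligibility. The article presents its criteria as the complete test: "Eligible patients will be those who fulfill all of the following inclusion criteria and who do not have any of the listed exclusion criteria". None of the four inclusion and seven exclusion criteria mentions past or current HTDJ or other herbal medicine. The frequency criterion reads "atrial fibrillation, seizure frequency ≥2 times a month (at least one ECG diagnosis" and sets no condition on what the patient was taking in that month.

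Timing. Research process record points says "the screening period (−3~0 days) will be 0 to 3 days before recruitment", and Table 3 puts baseline at day 0 with no run-in. Treatment history is collected at screening, but no rule uses it.

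Herbal medicine during the trial. Interventions says: "Participants will take one bag twice a day for 4 weeks, while avoiding oral administration of other Traditional Chinese Medicine for efficacy evaluation". For follow-up it says: "Then, do not accept Traditional Chinese Medicine, only western medicine treatment, followed up for 8 weeks". It is silent on the time before day 0. It also states that the placebo is one-tenth crude HTDJ.

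Outcome. The primary outcome is attack frequency at weeks 4, 8 and 12 against baseline, in four ordered grades by percent change.

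**The concern.** The stated objective is to evaluate HTDJ added to western medicine. That needs a baseline from before HTDJ. The plan allows a patient who takes HTDJ up to day 0 to enter, and that patient's baseline is then an on-treatment value. Randomisation to HTDJ changes little for this patient, while randomisation to placebo cuts the herbal exposure sharply. At weeks 8 and 12, when nobody is to take herbal medicine, prior users in both arms are compared off treatment with an on-treatment baseline.

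Use of other herbal products before day 0 raises a related problem: the baseline reflects a treatment that both arms then stop.

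At stake are the meaning of the primary result and the trial's power. Randomisation balances prior users between arms on average, but it does not turn their contrast into the effect of starting HTDJ. By barring other herbal medicine so that efficacy can be judged, the plan accepts that such use disturbs the assessment. It protects the follow-up values but not the baseline.

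**Working it through.** **1. Can a current user enter?** The criteria are presented as complete and contain no herbal-use rule. The herbal bar starts with study treatment. At most 3 days separate screening from recruitment, and nothing requires those days to be free of herbal medicine. As written, the answer is yes.

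**2. The plan's own figure.** Inputs from Sample size: 91.1% and 53.3% total efficacy, α = 0.025 (taken as one-sided), β = 0.2, superiority margin 10 points, 30 per group.

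- Planned difference: 91.1 − 53.3 = 37.8 points.
- n = (1.960 + 0.842)² × [0.911 × 0.089 + 0.533 × 0.467] / (0.378 − 0.10)² = 7.849 × 0.3300 / 0.0773 = 33.5, so 34 per group. The stated 30 is not reproduced.
- 30 / (1 − 0.2) = 37.5, so 38 per group and 76 in total, as stated.
- Power at 30 per group: standard error √(0.3300/30) = 0.1049; 0.278/0.1049 − 1.960 = 0.691; power 0.755.

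The gap between 30 and 34 is a separate matter. The value 0.755 serves here only as the starting point.

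**3. Effect of prior users on the total efficacy rate.** The article does not define this rate. I assume it pools the two best grades. Let f be the share of prior users and d the between-arm difference among them, in points. Then

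D(f) = (1 − f) × 37.8 + f × d.

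The documents give neither f nor d, so the values below are assumptions. Power is at 30 per group with the 10-point margin, using the formula in step 2.

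| Assumed response of prior users (HTDJ / placebo) | d | f = 10% | f = 20% | f = 30% |
|---|---|---|---|---|
| Equal (53.3% / 53.3% for power) | 0 | 34.0 points, power 0.59 | 30.2, 0.43 | 26.5, 0.29 |
| 20% / 0% | 20 | 36.0, 0.63 | 34.2, 0.53 | 32.5, 0.45 |
| 53.3% / 20% | 33.3 | 37.4, 0.70 | 36.9, 0.66 | 36.4, 0.62 |

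Example for the first row at f = 20%: 0.8 × 37.8 + 0.2 × 0 = 30.2. For the second row: 0.8 × 37.8 + 0.2 × 20 = 34.2. The difference in the first row needs only equal response in the two arms, whatever its level. The formula shows dilution whenever d is below 37.8 points. A d above that would inflate the difference.

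**4. Effect on the ordered grades.** Statistical analysis provides a rank sum test for ordered data, which could be applied to the four grades. Take assumed counts of 4 attacks a month off HTDJ and 2 on it. The patient qualifies at 2. If the count stays at 2 on continued HTDJ, the fall is 0% and the grade is Invalid. If it rises to 4 on placebo, the change is (4 − 2)/2 = +100% and the grade is Deterioration. Neither patient counts as a response in step 3, but a rank comparison places the HTDJ patient higher. Worsening after the switch would then count as HTDJ benefit.

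**The case against.** Enrolment of current users is inferred, not stated. The Introduction's remark on long-term use goes on to say that the experience is confined to individual cases, and a share near zero cannot be ruled out. The seventh exclusion, a catch-all for patients whose response cannot be assessed, together with the treatment history, would let an investigator turn current users away. The full protocol, version 2.0, is not shown and may deal with the matter. These points limit how large the problem can be said to be. They do not close the gap: the catch-all names no prior treatment and gives staff no rule, and the article offers its criteria as the full test.

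A reader might infer more than the documents support:

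- *That prior users cannot improve further.* They must still have at least 2 attacks a month, they receive western medicine, and the plan expects 53.3% response in its control group.
- *That placebo means complete withdrawal.* It contains 10% crude HTDJ, so during the 4 treatment weeks the change is a reduction.
- *That the gap creates a false-positive result.* Prior users are balanced on average, and on the total efficacy rate dilution is the likelier effect.
- *That the baseline is a count over the preceding month.* A month appears only in the entry criterion; no counting window is defined for the outcome.
- *That long-term users would recognise the granules.* Nothing says that they took this preparation or that it differs in taste from the placebo.

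**Conclusion.** The concern holds as a gap in the stated design. The plan admits current users of HTDJ or other oral herbal medicine, and for current HTDJ users the primary comparison does not estimate the effect of adding HTDJ. That rests on the text alone.

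The size is conditional. At assumed shares of 10% to 30%, the planned 37.8-point difference falls to between 34.0 and 26.5 points if prior users respond equally in both arms, and by less if those on placebo do worse. The net direction is not fixed: dilution is likely on the total efficacy rate, while a comparison of ordered grades could credit HTDJ with worsening after the switch. With the share unknown and the effects opposed, this should be corrected, but it is not shown to invalidate the trial.

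**What to change.** 1. For participants still to be enrolled, add a criterion excluding anyone who used oral HTDJ or other Chinese herbal medicine during the period over which the baseline attack frequency is counted, and state that period. Nobody should be asked to stop treatment in order to qualify.
2. For all randomised participants, code pre-baseline HTDJ and other herbal use from the treatment history recorded at screening, blind to allocation, and report the numbers by arm. If that history does not separate herbal from other treatment, say so.
3. Prespecify a sensitivity analysis of the primary outcome excluding prior users. Prior use is fixed before randomisation, so leaving these patients out keeps the comparison randomised.

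The cost is one eligibility line, one coded variable and one analysis. Enrolment would be slightly slower. The sensitivity analysis would be smaller: at an assumed 20% share, 30 evaluable per group becomes 30 × 0.8 = 24. The article appeared in October 2021 and recruitment was due to end on January 1, 2022, so the criterion can reach few participants. Steps 2 and 3 carry most of the value.

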### Outcomes

#### Primary outcome

Frequency of atrial fibrillation attacks (from baseline to weeks 4, 8, and 12)
° Significant effects: The frequency of attacks decreased by more than 70%.° Effective: The frequency of attacks decreased between 30% and 70%.° Invalid: The frequency of attacks decreased by less than 30%.° Deterioration: Increased attack frequency.

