**Method:**

This study adopts a randomized double-blind, single-simulated, placebo-controlled research method. Participants were randomly assigned in a 1:1 ratio through a centrally controlled, computer-generated, simple randomization schedule. Participants would take the medicine for 1 month, and the curative effect would be evaluated. Subsequently, the participants would not take TCM and only receive western medicine treatment. They would be followed up for another 8 weeks, and a clinical evaluation would be conducted. The secondary outcomes include echocardiography, Hamilton Anxiety Scale, Hamilton Depression Scale, rate of increase and decrease of anti-arrhythmia western medicine, the MOS 36-item short-form health survey, N-terminal-pro hormone B-type natriuretic peptide level, and integral TCM syndrome score. Adverse events will be monitored throughout the trial. Cases are from outpatient and inpatient with atrial fibrillation in the Cardiology Department of Longhua Hospital. Evaluations will be conducted at baseline and at weeks 4 and 12 after randomization.

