### Sample size

The sample size of this study was calculated based on the analysis of data published in previous articles on the treatment of atrial fibrillation by Chinese medicine and the expected value of efficacy. It was assumed that the total efficacy rates in the study and control groups were 91.1% and 53.3%, respectively [8]. The set *α* = 0.025, *β* = 0.2, superiority limit value*δ*= 10%, and the sample size of each group will be calculated as 30 cases, considering a 20% loss to follow-up, that is, a total of 76 cases.

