### Statistical analysis

All data are entered using excel worksheets, and SPSS22.0 statistical software is used for statistical analysis. For measurement data, *t* tests are performed for those that conform to the normal distribution, and the data are represented by the mean ± standard deviation; the row-rank conversion that does not conform to the normal distribution For non-parametric test, the data are represented by M (QR). The constituent ratio data uses the *χ*^2^ test. The one-way ordered data uses the rank sum test. *P*>0.05 is not statistically significant, and *P*<0.05 is statistically significant, two-sided test.

To further clarify the research conclusions of this clinical trial, we will perform subgroup analysis by gender or age in the future.

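### The primary outcome is listed at weeks 4, 8 and 12 with no primary time point, and the sample size is tied to none of them

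*Protocol article*

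**What the plan says.** Under Primary outcome, the article gives "Frequency of atrial fibrillation attacks (from baseline to weeks 4, 8, and 12". Four response classes follow, beginning with "Significant effects: The frequency of attacks decreased by more than 70" per cent. No class is attached to a visit. Table 3 schedules attack frequency at baseline and at all three later visits.

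Under Sample size: "It was assumed that the total efficacy rates in the study and control groups were 91.1% and 53.3%, respectively". That is one comparison of two rates, again with no visit named.

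Under Statistical analysis, tests are listed by type of data (t test, non-parametric test, chi-square, rank sum). The general rule is that P below 0.05 "is statistically significant, two-sided test". No method that takes the three visits together is mentioned.

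The abstract's Method paragraph comes closest to naming a main time point: "Participants would take the medicine for 1 month, and the curative effect would be evaluated". It then describes a second clinical evaluation after eight further weeks on western medicine alone. Neither evaluation is called primary.

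The article is also not consistent about week 8. The outcome section and Table 3 include it for attack frequency. The abstract and the prose under Research process record points give only weeks 4 and 12.

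**The concern.** A primary outcome needs a time point. Here three are given and none is chosen, while the sample size supports one comparison. Two things follow.

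First, the visits cannot stand in for one another. Study treatment lasts four weeks. Week 4 therefore measures the effect at the end of treatment, and weeks 8 and 12 measure whether anything persists after stopping. If week 4 were negative and week 12 positive, or the reverse, nothing in the article would say whether the trial had met its primary objective.

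Second, with no rule fixed, the visit with the most favourable result could be reported as the primary one. The chance of a false-positive claim would then exceed the stated 5%.

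**Working it through.** **1. The plan's own figure.** The article states 30 per group and 76 in total after 20% loss. The loss step reproduces: 30 / 0.8 = 37.5, rounded up to 38, and 2 × 38 = 76. The 30 itself does not follow from the usual formula with the stated inputs (91.1%, 53.3%, margin 10 points, α = 0.025 read as one-sided, power 80%):

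- variance term: 0.911 × 0.089 + 0.533 × 0.467 = 0.330
- difference beyond the margin: 0.911 − 0.533 − 0.10 = 0.278
- n per group = 0.330 × (1.960 + 0.842)² / 0.278² = 33.5, so 34

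This gap is a side note, and the present point does not depend on it. What matters is that the calculation contains one comparison and no visit.

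**2. What the text fixes about the primary comparison.**

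| Element | Where | Visit fixed? |
|---|---|---|
| Outcome definition | Primary outcome | Three listed, none chosen |
| Response classes | Primary outcome | None |
| Assumed rates | Sample size | None |
| Tests and level | Statistical analysis | None |
| Evaluation of curative effect | Abstract, Method | After one month of treatment, not called primary |
| Success rule across visits | Nowhere | – |

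**3. False-positive rate if any one visit suffices.** Inputs: three tests, each two-sided at 0.05 (Statistical analysis), and no true effect at any visit. The common correlation r between the visit-wise test statistics is an assumption, because the article gives none.

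- Independent visits (r = 0): 1 − 0.95³ = 0.1426, and 0.1426 / 0.05 = 2.85.
- Correlated visits: the probability that at least one of three standard normal statistics with equal correlation r exceeds 1.96 in absolute value, by numerical integration.

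| Assumed r | P(at least one P < 0.05) | Ratio to 5% |
|---|---|---|
| 0 | 14.3% | 2.9 |
| 0.3 | 13.6% | 2.7 |
| 0.5 | 12.5% | 2.5 |
| 0.7 | 10.9% | 2.2 |
| 0.8 | 9.8% | 2.0 |
| 0.9 | 8.4% | 1.7 |

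The Bonferroni bound, which holds whatever the correlation, is 3 × 0.05 = 15%. If only weeks 4 and 12 counted, as the abstract's schedule might suggest, the independent case is 1 − 0.95² = 9.75%.

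**4. The opposite rule.** If all three visits had to be significant in the same direction, the false-positive rate would be 0.3% at r = 0.5 and 2.3% at r = 0.9, well below 5%. The size of the error therefore depends on a rule the article does not state.

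**5. What the remedies cost.** With one named time point, the error rate is the stated level and multiplicity adds no patients. If all three visits stayed primary with Bonferroni (one-sided 0.025 / 3), the article's own rates and margin would give 0.330 × (2.394 + 0.842)² / 0.278² = 44.7. That is 45 evaluable per group, 45 / 0.8 = 56.25, so 57 per group and 114 in total. At that level the power would be about 60% with 30 per group and 72% with 38.

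**The case against.** The strongest reply is that multiplicity handling is usually left to a statistical analysis plan, that none is shown here, and that the article condenses a longer protocol. This stands for the adjustment procedure: its absence is not a fault in this document. It does not cover the time point. The article states the time points of its primary outcome, gives three, does not choose, and then sizes the trial on rates tied to none.

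A second reply is that the text names one outcome assessed at three times, not three primary tests. This also stands. A reader might infer that each visit is declared primary and tested separately at 5%, but the statistical section is a general list by type of data and does not say how the primary outcome is tested.

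A reader might also infer that the plan simply carries an inflated error, say 2.5 times nominal. The documents do not support that. The ratio holds only near a correlation of 0.5, which they do not give. It is not an upper limit, since independence gives 2.9. It also requires that any one visit be enough, whereas a rule requiring all three would be conservative.

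Finally, the later visits serve a declared aim, because the objectives ask for medium-term as well as short-term evidence. That is a reason to keep weeks 8 and 12 in the plan with a defined role. It does not settle which visit decides the trial.

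**Conclusion.** The concern holds as a fault in how the primary outcome is fixed: no primary time point, no success rule across visits, and a sample size attached to none of the three. That part needs no assumption.

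The size is conditional. If significance at any visit counted as a positive trial, the false-positive rate would be about 8% to 14%, or 1.7 to 2.9 times 5%. This assumes no true effect, two-sided 5% tests at each visit and a common correlation between 0.9 and 0. The interim look at 44 participants is a separate matter and is not included in this range. The point should be corrected, and doing so is cheap.

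**What to change.** In Primary outcome, name one primary time point, and in Sample size say that the 91.1% and 53.3% rates refer to it. Week 4, the end of treatment, agrees with the abstract, which places the evaluation of the curative effect after the month of treatment.

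In Statistical analysis, state that week 8 and then week 12 are tested in that fixed order, each at two-sided 5%, only if week 4 is significant. Otherwise they are reported descriptively in support of the medium-term objective. Bring the abstract and the visit prose into line with Table 3 on whether attack frequency is assessed at week 8.

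The choice must be made and dated before any unblinded comparative results are seen. Recruitment began in April 2020 and the article describes an analysis at 44 participants, so the amendment should state what was known when the choice was made.

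The cost is a sentence or so in each section. Weeks 8 and 12 lose primary status, and multiplicity adds no patients. Co-primary visits with adjustment would also remove the ambiguity, but with Bonferroni they would need 114 participants instead of 76 on the article's own assumptions.
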